## Abstract

Developing postadoption interventions to prevent parenting stress and promote parents’ well-being is urgent. Mindful parenting-based interventions show promise in achieving these goals and are well received by adoptive parents (APs). However, face-to-face interventions face significant barriers. E-health tools offer a solution by improving accessibility and flexibility and reducing long-term costs. Our main aim is to develop and assess the preliminary efficacy of a web-based mindful parenting postadoption intervention, *AdoptMindful2Care@Web*, by using a user-centered approach to ensure its effectiveness and cost efficiency. First, two quantitative surveys will be conducted to assess the needs and preferences of APs and gather input from adoption professionals. Then, a prototype version of the intervention will be created and tested for usability with the APs via the Think-Aloud method. Finally, a pilot version will undergo a two-arm pilot randomized controlled trial to assess its feasibility, acceptability, and preliminary efficacy via self-report questionnaires. By developing *AdoptMindful2Care@Web* employing a user-centered approach, we hope to provide an effective intervention that is adjusted to the reality of its users and the surrounding context. In doing so, we will be able to promote AP access to specialized mental health care efficiently.

## 1. Introduction

Adoptive parents seem to be particularly vulnerable to depression, anxiety, stress, and difficulties in being emphatic, sensitive, and efficient in managing children’s behavior [1]. Such parents are obliged to address adoption-related issues (e.g., experiences with infertility, increased likelihood of parenting children with preexisting behavioral/emotional difficulties, and stigma attached to adoption [2,3,4]), which can place them in a more vulnerable position with respect to these mental health issues than nonadoptive parents. This is a particularly concerning reality, since it is thoroughly reported in the literature that these challenging circumstances can compromise children’s development and adoption stability [5]. However, in Portugal, there are no structured governmental postadoption services yet available, although a legal framework for the provision of postadoption support was set out in 2015 [6]. Similarly, there are no evidence-based psychological interventions specifically designed to promote adoptive parents’ well-being and positive parenting available in our country.

Worldwide, postadoption therapeutic services, when available, are usually focused on children’s difficulties, parents’ ability to manage children’s behavior, and parent-child relationship quality within an attachment framework [7,8,9]. These interventions are indispensable, but they are not designed to incorporate parents’ needs in coping with the emotional challenges of parenthood or in achieving greater nonjudgmental acceptance of and compassion for the self and the child, or self-regulation of immediate emotional states in favor of long-term goals that sustain the parent-child relationship [10]. These factors may be crucial targets for reducing parenting stress, promoting positive parenting, and thus improving families’ well-being [11,12].

Mindful parenting interventions (MPIs) are focused on the targets mentioned above [13] and are highly acceptable among adoptive parents, as well as promising in promoting both adoptive parents’ and children’s well-being [14,15,16]. However, insurmountable barriers arise when planning the face-to-face provision of such interventions in Portugal. This issue is related to the fact that in Portugal, 18 social security district centers (SSDCs) ensure postadoption support in different geographic reference areas; each one has coordinated but independent organizational structures and procedures, serves heterogeneous populations, and faces specific time, material, and human constraints in providing postadoption support. Regarding therapeutic interventions specifically, several shared constraints can be noted: (1) severe discrepancies in the number of adoptions carried out in each SSDC, high geographic dispersion, and different adoption timings among adoptive families, for example, constrain establishing face-to-face therapeutic group formats, and (2) severe time, material, and human limitations and reduced expertise in therapeutic care by the adoption teams constrain the individual face-to-face application of MPIs [17]. These circumstances call for alternative delivery formats.

E-mental health (e-mhealth) tools (i.e., the use of information technologies to deliver mental health services at a distance [18])—namely, web-based interventions (i.e., self-guided treatments delivered via websites and designed to educate and/or cause therapeutic change [19])—are an innovative form of intervention and seem to be a promising option to overcome most of the noted barriers, particularly given their many benefits: (1) improved access to care, since health care can become available regardless of time and place, contributing to health care equity and removing thresholds such as stigmatization; (2) empowerment, giving people the opportunity to take greater control of their own health care by enabling them to choose when and where they want to access it; (3) innovation, since these technologies open up a wide range of possibilities for health care and can provide the groundwork for sustainable changes; and (4) quality of care, owing to highly efficient and innovative systems and to effective interventions that lower costs and increase safety by reducing human errors [20]. These tools are already being used with adoptive parents in other countries [21,22]; however, none of them were specifically designed to help adoptive parents deal with the emotional challenges of parenthood or adopt mindful parenting practices; additionally, they are not prepared to be used in environments other than those for which they were designed—which makes their replication in the Portuguese context unfeasible. However, these interventions may offer valuable insights into features that should be considered in the development of a new intervention of this nature [23,24].

The development of e-mhealth tools is a complex process that requires a user-centered approach to incorporate the requisite people–context–technology interrelationships, i.e., several steps must be followed during content and technological feature development with the active participation of prospective users and other key stakeholders [20]. According to the guidelines of the Management Centre for e-Health Research and Disease (CeHRes) Roadmap [25,26], a reliable and useful product is directly dependent on the contextual inquiry, value specification, and design phases, since they enable the understanding and incorporation of the physical–social–cultural environment and the needs and preferences of prospective users, funders, and policy-makers that the product should serve through its content and technological features. This work is even more important when few studies have been performed with prospective users, as is the case for Portuguese adoptive parents [20,27].

By developing and preliminarily testing the efficacy of a web-based mindful parenting postadoption intervention, *Adoptindful2Care@Web*, employing a user-centered approach, our project intends to respond efficiently to the urgent need to improve adoptive parents’ access to specialized mental health care [28]. To better ensure *Adoptindful2Care@Web* suitability, usefulness, efficacy, and cost-effectiveness, adoptive parents and adoption professionals will be involved throughout the entire development (i.e., contextual inquiry, value specification, and design) and preliminary evaluation process. Here, we describe the study protocol for the content and technological feature development and the preliminary efficacy assessment of *AdoptMindful2Care@Web*.

## 2. Materials and Methods

### 2.1. Design

*AdoptMindful2Care@Web* will be developed following the CeHRes Roadmap and by adapting the structure of its standard version (*AdoptMindful2Care*; [29]) according to the results of the current protocol.

*AdoptMindful2Care* is an eight-session, face-to-face group intervention in which adoptive parents learn to apply mindfulness and self-compassion skills to themselves and to their parenting experience. This intervention was built on the basis of the Mindful Parenting Program manual [13]. The following topics are covered: (1) automatic pilot parenting, (2) beginner’s mind parenting, (3) reconnecting with our body as a parent, (4) responding versus reacting to parenting stress, (5) parenting patterns and schemas, (6) conflict and parenting, (7) love and limits, and (8) a mindful path through parenting.

In *AdoptMindful2Care@Web*, we intend to keep the same content (each topic will correspond to a module), adapting its presentation format (e.g., through videos recorded by psychologists, audios, interactive texts, and interactive exercises) according to the results obtained in the exploratory studies we will conduct at the beginning of the project (Studies 1 and 2).

The CeHRes Roadmap [11] provides an evidence-based development approach for e-health interventions. It states that the development of an e-health intervention must incorporate the contributions of prospective users and other stakeholders throughout the entire creation and pre-testing process, which includes the contextual inquiry, value specification, and design phases. By creating a good fit among the human, technological, and contextual factors, this holistic approach can increase the degree to which an intervention reaches its goals. The development of *AdoptMindful2Care@Web* will be guided by a user-centered approach, which will rely on the active participation of adoptive parents—as its future users—and professionals working in adoption teams—as expected mediators of access to the intervention—through the entire process (Figure A1).

To achieve this goal, the present study protocol will be divided into three phases:
Phase I, which will be dedicated to contextual inquiry and value specification tasks. In turn, this phase is divided into two distinct but complementary studies:
oStudy 1, performed with adoption professionals, will use a survey developed by the research team for this purpose and is intended to explore the recommendations of such professionals regarding the content, format, and dissemination features required for AdoptMindful2Care@Web to meet (1) the needs expressed by adoptive parents when asking for professional support, (2) the professionals’ own needs when providing support for adoptive parents, and (3) the adoption system’s ethical and institutional requirements for the integration of AdoptMindful2Care@Web in the organizational structure and working routine of adoption services.oStudy 2, performed with adoptive parents as prospective users of AdoptMindful2Care@Web, will use a survey developed by the research team for this purpose to (1) characterize the literacy of adoptive parents regarding e-mhealth tools, (2) identify the mental health and parenting needs that such parents expect to be addressed by AdoptMindful2Care@Web, and (3) analyze the preferences and acceptance (perceived utility and availability for use) of such parents regarding AdoptMindful2Care@Web’s content, format, and dissemination features.Phase II, which will be dedicated to the design task. In this phase, the prototype of *AdoptMindful2Care@Web* will be developed on the basis of the information gained in Phase 1. The intervention’s content will be developed by the research team and systematically and interactively reviewed by researchers/clinicians in the adoption field. Technological features will be developed by a specialized IT company according to the guidance of the research team. This process will be monitored by LAICOS–Behavioral Change, a company specialized in behavioral science. In this phase, we will also perform Study 3, which is intended to test the usability of the prototype version of *AdoptMindful2Care@Web* with adoptive parents, using the Think-Aloud Protocol and a survey developed by the research team for this purpose.Phase III, which will be dedicated to operationalization and preliminary summative evaluation. The pilot version of *AdoptMindful2Care@Web* will be developed on the basis of the results of the previous phase. Then, we will perform Study 4, which is intended to assess the feasibility, acceptability, and preliminary efficacy of the intervention (i.e., improvements in parent and child outcomes at postintervention and/or follow-up) through a two-arm pilot randomized controlled trial. The results of this study will inform the necessary changes to be incorporated into *AdoptMindful2Care@Web* to establish its final version.

See Figure 1 for a detailed overview of the study protocol.

### 2.2. Participants

The participants in Study 1 will be professionals who will have worked in Portuguese adoption services for at least 2 years.

In Studies 2, 3, and 4, the participants will be adoptive parents. To be eligible, parents will have to have (a) at least one adoptive child aged under 18 years; (b) no other adoption process in progress; (c) reading and writing abilities in the Portuguese language; and (d) regular access to the internet and electronic devices. In Studies 3 and 4, parents will be excluded if they will have been diagnosed with a serious mental health condition (e.g., schizophrenia).

### 2.3. Materials

The instruments used and the respective outcomes measured are presented in Table 1.

### 2.4. Procedure

This three-phase, multimethod study protocol is supported by the Portuguese Foundation for Science and Technology through a doctoral grant. It is part of a larger project hosted in the Faculty of Psychology and Education Sciences of the University of Coimbra and supported by the Calouste Gulbenkian Foundation. It will be carried out with the collaboration of scientific and community institutions active in the fields of adoption and parenting and of all the Portuguese adoption agencies. The data are planned to be collected up to May 2026.

For Studies 1, 2, and 4, self-report surveys provided by a secure online survey tool of the host institution (LimeSurvey^®^) will be used. Data will be stored on this platform in accordance with all relevant confidentiality and privacy rules. For Study 3, the Think-Aloud Protocol method will be used.

Participants will be recruited through adoption agencies. Potential participants will be selected by these agencies, which will subsequently send an e-mail to them (written by the research team).

In Studies 1 and 2, the e-mail will contain summary information about the objectives of the study and the researchers’ contacts, as well as the link to the online survey. The survey is estimated to take an average of 30 min to complete. The participants will be able to interrupt completion at any point and resume later by creating their own access credentials. E-mails will be sent to participants whose survey has been incomplete for 1, 2 and 4 weeks, reminding them to complete it and offering them the opportunity to recover their access credentials if they have lost them.

For Study 3, the e-mail will contain the link to the form with information about the objectives of the study. Through this link, respondents can express their interest in participating, provide their contact details, and provide permission to be contacted by the research team to schedule the session. The sessions will take place in person in a space belonging to the university that hosts the project. The participants will have access to a computer on which the intervention platform will be made available. They will be instructed to guide their own use of the platform—with the aim of bringing this experience closer to its real use—while simultaneously receiving an opportunity to express their thoughts about it. If needed, the participants will be prompted to keep talking during the session. Video and audio recordings will be made, and written notes will be taken throughout the sessions for later analysis. To augment the information obtained during this task with a quantitative aspect, participants will also be asked to complete a self-report questionnaire at the end of the session.

In Study 4, an e-mail will contain a link to a website where interested respondents can find detailed information about the project and the intervention and through which they can complete a request to be contacted by the research team. This contact phone call will be used to explain the study and the intervention in more detail, answer questions, and verify eligibility. After eligibility is confirmed, the participants will be randomized into two groups: an experimental group, with immediate access to *AdoptMindful2Care@Web*, and a control group, with access to the intervention only at the end of the study. In both groups, participants will have to complete online self-report questionnaires, the link to which will be sent via e-mail, at three different times: T0 (preintervention), T1 (postintervention; for participants in the experimental group, the link will be sent 2 days after completing the last module of the intervention, and for the waiting group, 8 weeks after completing the T0 step), T2 (1-month follow-up), and T3 (2-month follow-up).

Informed consent will be obtained from all participants in the four studies after they have read the information provided about the research project, the inclusion criteria, the researcher’s duties, the participant’s rights, and the data protection policy used for data storage. In Studies 1, 2, and 4, consent will be obtained electronically by the participant selecting the option “Yes, I authorize”. In Study 3, written consent will be obtained.

The participants in the four studies will receive no financial compensation.

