### 2.6. Ethical Considerations

This project involves human participants and the collection/processing of personal data.

Ethical approval from the Faculty of Psychology and Education Sciences of the University of Coimbra has been obtained (CEDI/FPCEUC: 83/R_9 on 17 January 2024).

Anonymity/confidentiality requirements and the relevant legal contingencies will be respected at all stages and comply with international (Declaration of Helsinki; European Legislation) and national (Code of Ethics of the Ordem dos Psicólogos Portugueses [OPP]) ethical and deontological standards for human experimentation. The data protection guidelines of the University of Coimbra, which are governed by General Data Protection Regulation (GDPR), will also be strictly followed.

All data collection processes will begin after informed consent has been obtained from all participants. As adoption is not definitive in Portugal during the first months of children’s placement with prospective adopters, sample collection will only occur after the adoption has been finalized in court so as not to interfere with the adopters’ decision.

The participants will be informed about the voluntary nature of their participation and their right to refuse to participate, to access/change/delete/restrict the processing of their personal data, or to withdraw at any time without penalty and justification. They will also be assured that their data (including confidential personal data) will be kept anonymous, stored in secure databases (to which only the research team will have access), used only for research purposes, and kept only as long as necessary for the study. This information will be detailed on the home page of the online survey (Limesurvey^®^) hosted on the host institution’s website.

Ethical issues related to RCTs will also be considered. Participants who are not eligible for inclusion in the study groups and need appropriate psychological intervention will be counseled and referred for specialized follow-up. Guiding documents on clinical trial disclosure and data protection in clinical research from the National Commission for Ethics in Clinical Research will also be considered. The pilot RCT will be registered at clinicstrials.gov.

Given the development and study of web-based interventions, the OPP Guidelines for the Provision of Information and Communication Technology (ICT)-mediated Psychology Services will also be followed.

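### Study 4 as written randomises parents before the T0 questionnaire, so the self-reported baseline may be given with knowledge of the arm

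*Protocol article*

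**What the plan says.** The Study 4 sequence is in the protocol article, section 2.4 (Procedure). An interested parent asks through a website to be contacted. Of the call that follows, the article says: "This contact phone call will be used to explain the study and the intervention in more detail, answer questions, and verify eligibility". The next step is: "After eligibility is confirmed, the participants will be randomized into two groups: an experimental group, with immediate access to" the intervention, "and a control group, with access to the intervention only at the end of the study". The assessments come after that: "In both groups, participants will have to complete online self-report questionnaires, the link to which will be sent via e-mail", at T0, T1, T2 and T3. The control arm's T1 is timed from T0, not from randomisation: "for the waiting group, 8 weeks after completing the T0 step". The experimental arm's T1 link follows completion of the last module.

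On consent, section 2.4 says: "In Studies 1, 2, and 4, consent will be obtained electronically by the participant" ticking an authorisation option. Section 2.6 (Ethical Considerations) places consent before data collection. It also says of the participants' rights and data-protection information: "This information will be detailed on the home page of the online survey". Neither section places consent relative to randomisation.

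Table 1 lists the efficacy outcomes at T0 to T3. All are questionnaires completed by the parent, including the two primary outcomes, parenting stress and positive mental health. Section 2.5 analyses them by repeated-measures ANOVA or linear mixed models with a time-by-group interaction over the four assessments.

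**The concern.** A baseline is protected from allocation only if it is recorded before the participant can know the arm. In the order written, it is recorded afterwards. One arm can start at once and the other must wait until the study ends, so the arm is plain to the parent. A parent who has just been told to wait, or who is about to start, may answer questions on stress and well-being differently for that reason.

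Two things are at stake. First, T0 is the reference for change over time, so a temporary shift in one arm at T0 looks like differential change later. It could go either way. A disappointed wait-list parent who reports more stress at T0 and then settles makes the control arm appear to improve. An experimental parent who reports more difficulty just before starting makes the intervention appear to work. Second, a parent who leaves after randomisation but before T0 has been allocated yet supplies no outcome data, and neither proposed model can recover a person with no observations.

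**Working it through.** **Order of events.** Side by side, the steps in section 2.4 are:

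1. Website request.
2. Call: explanation, questions, eligibility.
3. Randomisation to immediate or end-of-study access.
4. E-mailed questionnaires in both arms, the first being T0.

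No sentence moves T0 ahead of step 3. The labels given to T0 (preintervention in section 2.4, baseline in the note to Table 1) place it before treatment, not before allocation. The article describes no concealment of the arm from parents. Section 3 mentions blinding only as something this pilot may help to optimise for a later trial.

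**Plan's own figure.** No figure in the article measures this problem. The sample size does not depend on it. Assuming f = 0.25 for the stated medium effect, correlation ρ = 0.5, no sphericity correction, alpha 0.05 and m = 3 measurements, λ = N·m·f²/(1−ρ) = 60 × 3 × 0.0625/0.5 = 22.5 on 2 and 116 degrees of freedom. This gives power 0.991, which matches the stated 60 participants at 0.99. Changing the order leaves that figure as it is.

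**Effect of a shift at T0.** Let knowledge of allocation move T0 in one arm by b (in SD units), and let a fraction p of the shift remain at the later assessment. The change-from-baseline contrast is then biased in size by b(1−p). With b = 0.2 (assumed):

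- p = 0: 0.2 × 1 = 0.2 SD
- p = 0.5: 0.2 × 0.5 = 0.1 SD
- p = 1: 0

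The bias is therefore at most 0.2 SD under this assumption, reached only if the shift is confined to T0.

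**Consequence for a test.** Assume no true effect, p = 0, ρ = 0.5 (so the SD of change is √(2(1−0.5)) = 1), a two-sided 5% normal test of change, and n per arm. The standard error is √(2/n), and the rejection rate is Φ(b/SE − 1.96) + Φ(−b/SE − 1.96).

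| Shift b | n = 30 per arm | n = 48 per arm |
|---|---|---|
| 0 | 5.0% | 5.0% |
| 0.1 | 6.7% | 7.8% |
| 0.2 | 12.1% | 16.5% |
| 0.3 | 21.3% | 31.2% |

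The 30 is the stated number per condition. The 48 is 96/2, assuming a 1:1 split of the recruitment target. The planned interaction test uses four assessments, so these rates illustrate scale and are not the trial's error rates.

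**Loss before T0.** If 5%, 10% or 20% of an arm of 48 never submitted T0 (assumed), 48 × 0.95, 48 × 0.90 and 48 × 0.80 leave about 46, 43 and 38 with data. Because the control T1 is timed from T0 completion, a wait-list parent with no T0 has no defined date for T1 either.

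**The case against.** The strongest reply is that the order is read from the layout of a paragraph. The article introduces the arms and then gives one schedule for both, and T0 is called preintervention. The article does not say when parents learn their arm, and a full protocol may fix that. This has some force: early disclosure is the natural reading but is not stated. It does not remove the point. The text places randomisation directly after eligibility, and nothing places T0 before it.

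A reader might also infer more than the article supports:

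- **Consent after randomisation.** The information on the survey home page, with T0 as the first Study 4 survey described, invites this reading. But that sentence covers the studies generally and says where information is shown. Detailed information is also offered on the Study 4 website before the call, and section 2.6 puts consent before any data collection. Consent could be taken before the call.
- **A one-for-one bias.** This holds only if the shift affects T0 alone. A reaction that persists cancels partly or wholly in the change contrast.
- **Losses that differ by arm.** Nothing in the article shows this, and promised access at study end is a reason for wait-list parents to stay.
- **Bias as a share of the expected effect.** The article says only that effects are medium and gives no standardised difference, so such a percentage would come from assumed inputs.

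Finally, this is a pilot, and loss before baseline would itself be a feasibility result. That lowers the severity. It does not justify keeping an avoidable weakness in the preliminary efficacy estimate or in procedures meant to inform a larger trial.

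**Conclusion.** The point holds as a risk built into the written sequence. Followed as printed, Study 4 collects a self- or parent-reported baseline after allocation in a wait-list trial with no stated concealment of the arm, and then uses that baseline in the time-by-group analysis. Adjusting for sociodemographic, clinical or child-related variables, as section 2.5 plans, would not remove a shift caused by knowing the arm.

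Neither the size nor the direction of any shift can be obtained from the article. The 0.2 SD figure is an illustration and an upper limit for a shift of that assumed size. The rejection rates and loss counts rest on the further assumptions listed with them. The timing of consent is unstated and should be stated; the article does not show it to be wrong. Severity: should-fix.

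**What to change.** Rewrite the Study 4 sequence in section 2.4 as: eligibility call; e-consent; T0 submitted; randomisation triggered by submission of T0; arm disclosed and platform access opened. Stating consent in the same sentence settles its place before randomisation. If this is already the intended procedure, only the wording needs correcting.

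The wait-list T1 can still be counted from T0 completion, and the sample size does not change. Parents who never submit T0 would then be counted as lost before randomisation and reported as a recruitment result, not as missing randomised participants. The cost is a reordering of steps, and parents learn their arm only after submitting T0.
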